### Methodology

On screening, patients will visit the trial unit after an overnight fast. After informed consent is obtained, subjects will be screened for eligibility to participate in the study. Screening will include a careful assessment of the inclusion/exclusion criteria and collection of blood and urine for screening tests. Subjects will give a full medical history, and undergo a full physical examination, including height, body weight, waist circumference and vital sign measurements. A 12-lead electrocardiogram (ECG) tracing will be obtained to screen for underlying cardiac disease. All subjects will receive life style instructions (normal diet,  $\leq 2$  alcohol consumptions a day, restriction on caffeine and grapefruit intake, no strenuous or unaccustomed exercise). If a patient is on oral metformin treatment, treatment will be discontinued until the end of the study. Subjects who meet all entry criteria will be eligible for randomization on Day 0.

On Day 0 patients will visit the trial unit after an overnight fast. The patients may be asked to present in CRU on Day -1 if required (for baseline investigations). At Day 0 (and/or Day -1), the following assessments will be performed: Physical examination, vital signs, height and body weight, waist circumference, clinical laboratory tests, urine collection (urinalysis), 12-lead ECG, AEs and change in concomitant medications will be reported, hyperinsulinemic euglycemic clamp (the clamp procedure is described in Appendix C) will be performed. Liver fat will be measured by 1H MRS. All patients will get life style instructions.

On day  $14 \pm 1$ , the patients will visit the trial unit after an overnight fast. The following assessments will be performed on day  $14 \pm 1$ : vital signs, height and body weight, waist circumference, safety clinical laboratory tests, urine collection (urinalysis), 12-lead ECG, AEs and change in concomitant medications will be reported, all patients will get life style instructions.

On Day  $28 \pm 2$ , patients will visit the trial unit after an overnight fast. At Day 28, the following assessments will be performed: physical examination, vital signs, height and body weight, waist circumference, clinical laboratory tests, urine collection (urinalysis), 12-lead ECG, AEs and change in concomitant medications will be reported, hyperinsulinemic euglycemic clamp (the clamp procedure is described in Appendix C) will be performed, liver fat will be measured by 1H MRS, discontinuation of study drug, all patients will get life style instructions.

At Day 35-38, patients will visit the trial unit after an overnight fast and the following assessments will be performed: physical examination, vital signs, height and body weight, waist circumference, safety clinical laboratory tests, urine collection (urinalysis), 12-lead ECG, AEs and change in concomitant medications will be reported, restart of oral metformin treatment (if applicable).

For subjects who are withdrawn, the above assessments should be performed within 8-10 days after the last drug administration.

---

---

**Benefit and risk**

This study does not have specific advantages for the study subjects. The results of this study may help researchers learn whether TRC150094 may be beneficial for the treatment of male subjects with increased cardiometabolic risk associated with non-traditional risk factors. [6,6-2H2] glucose is glucose labeled with a stable isotope of hydrogen, which behaves as the natural substrate and has no side effects. [1,1,2,3,3-2H2] labelled glycerol is glycerol labeled with 5 stable isotope of hydrogen, which behaves as the natural substrate and has no side effects. Actrapid is fast acting insulin, a hormone that could induce hypoglycemia. However, it is not in the scope of this protocol to allow hypoglycemia to occur, since plasma glucose concentration will be fixed at 5 mmol/l by a variable infusion of glucose 20% guided by frequent bedside glucose measurements. An overview of the blood samples and blood volumes taken during the study is provided in Table 1. The total blood volume to be withdrawn from any individual subject will be 391.2 ml for subjects at Veeda Clinical Research, India and 361.2 ml at AMC, Netherlands. This amount is not considered to be of negative influence to the subject's health. A possible side effect of clamping, which is very rare and mostly preventable, could be hypoglycaemia. MR- spectroscopy of the liver will be made which takes about 30 minutes. This spectroscopy is not considered to be potentially harmful to subjects.

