### 6.3 Exclusion Criteria

Subjects will not be considered eligible for entry in the study if they meet one or more of the following criteria.

1. Medical history, physical examination, vital signs, clinical laboratory tests, 12-lead ECG and Chest X ray (in India only) with any significant abnormalities, in the opinion of the investigator.
2. Subjects with any known somatic illness, including neoplasm, endocrine disorder such as cushing's disease, PCOD and uncontrolled hypothyroidism, neurologic disorder, active infection, or recent surgical procedure within 3 months of the study initiation.
3. Subject currently using medication, which can influence glucose or FFA metabolism such as fibrates, niacin, ACE inhibitors (subjects are not excluded in case of use of a stable dose for at least 6 weeks prior to baseline measurement, taking (ACE) inhibitors (ACE-I) or angiotensin-receptor blockers (ARBs)), PPAR agonists, omega 3 fatty acids.
4. eGFR < 60 mL/min/1.73m^2 at screening as evaluated by Modification of Diet in Renal Disease (MDRD) method.
5. History of angina, Myocardial Infarction (MI) or stroke since last 6 months.
6. Hypertension with SBP/DBP  $\geq$  160/100 mm Hg at screening.
7. ALT or AST  $\geq$  ULN\*3 at screening
8. History or presence of malignancy.
9. History of recreational drug use within the last 30 days, or regular consumption of greater than 2 units of alcohol/day
10. History of allergy to the test drug or any drug chemically similar to the drug under investigation.
11. Seropositive for Hepatitis B, Hepatitis C or HIV.
12. Subjects suffering from any psychiatric (acute or chronic) illness.
13. Intake of any medication except those permitted in this study (see Section 6.6).
14. Intake of any investigational drug in the period within 3 months prior to the first dose of study drug.

- 
15. History of significant blood loss due to any reason, including blood donation, in the 12 weeks prior to the first dose of study drug; or the total blood loss in the last 3 months, including for this study, exceeds 450 mL.
  16. History of any bleeding disorder.
  17. Existence of any surgical or medical condition which, in the judgment of the principal investigator, might interfere with the absorption, distribution, metabolism or excretion of the study drug or might be likely to compromise the safety of the subject.

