**8.5.1 . Clinical laboratory tests**

A blood sample will be taken for measurement of haematology and biochemistry parameters, and a urine sample will be taken for urinalysis at the following time points:

- screening visit
- Day 0
- Day 14
- Day 28

- 
- Day 35

The Laboratory parameters and time-points are specified in (Appendix A) and (Appendix B).

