### **11.3 Benefits and risks assessment, group relatedness**

This study does not have specific advantages for the study subjects. The results of this study may help researchers learn whether TRC150094 may be beneficial for the treatment of male subjects with the metabolic syndrome. The most important known adverse event of TRC150094 is headache. [6,6-2H2] glucose is glucose labelled with a stable isotope of hydrogen, which behaves as the natural substrate and has no side effects. [1,1,2,3,3-2H2] labelled glycerol is glycerol labelled with 5 stable isotope of hydrogen, which behaves as the natural substrate and has no side effects. Actrapid is fast acting insulin, a hormone that could induce hypoglycemia. However, it is not in the scope of this protocol to allow hypoglycemia to occur, since plasma glucose concentration will be fixed at 5 mmol/l by a variable infusion of glucose 20% guided by frequent bedside glucose measurements. An overview of the blood samples taken during the clamp is provided in Appendix B. The total volume of blood sample is 361.2 ml for AMC subjects and 391.2 ml for Indian subjects. This amount is not considered to be of negative influence to the subject's health. MR- spectroscopy of the liver will be made which takes about 30 minutes. This spectroscopy is not considered to be potentially harmful to subjects. An X-thorax will be performed

---

during the screening visit, to exclude TB-infection, in patients in India only. The radiation hazard of the X-thorax is 0.02 milliSievert per X-ray. For comparison: background radiation is 2 milliSievert per year for every person.

Incentives: In the Netherlands patients will receive 100 euro for each study visit (not screening), this includes reimbursement for travel costs.

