| Endocrinology
Thyroid Profile (T3, T4, fT4, TSH)                                                                                                                                                                                                          |                                                                                                                                                                                                                                                                    |
| Urinalysis
pH, specific gravity, ketones, protein, glucose, urobilinogen, bilirubin, nitrite, erythrocytes, leukocytes                                                                                                                                    |                                                                                                                                                                                                                                                                    |
| Viral serology
HBsAg, hepatitis C antibody, HIV I, HIV II                                                                                                                                                                                                 | Lipid Parameters
Total cholesterol, TG,
LDL – Cholesterol, VLDL, HDL                                                                                                                                                                                  |
|                                                                                                                                                                                                                                                                     | Drugs of abuse
amphetamines, barbiturates,
benzodiazepines, cannabinoids, cocaine, opiates, methadone
Alcohol breath test                                                                                                                   |

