**Time points for the clinical laboratory tests are mentioned in Appendix B.**

**APPENDIX B: Study visits.**

| 1                                        | S | Day 0 |         |         |         |                                   |      |      |      |      |                                   |      |      |      |      | Day 14 | Day 28 | Day 35 |
|------------------------------------------|---|-------|---------|---------|---------|-----------------------------------|------|------|------|------|-----------------------------------|------|------|------|------|--------|--------|--------|
|                                          |   | 0 min | 115 min | 120 min | 125 min | During clamps                     |      |      |      |      |                                   |      |      |      |      |        |        |        |
|                                          |   |       |         |         |         | Last 20 mins (at 5 min intervals) |      |      |      |      | Last 20 mins (at 5 min intervals) |      |      |      |      |        |        |        |
| Invest                                   | T | -2:00 | -0:05   | 0:00    | 0:05    | 1:50                              | 1:55 | 2:00 | 2:05 | 2:10 | 4:00                              | 4:05 | 4:10 | 4:15 | 4:20 |        |        |        |
| Informed consent                         | × |       |         |         |         |                                   |      |      |      |      |                                   |      |      |      |      |        |        |        |
| Demographics, smoking status             | × |       |         |         |         |                                   |      |      |      |      |                                   |      |      |      |      |        |        |        |
| Height, weight, BMI, Waist Circ          | × | ×     |         |         |         |                                   |      |      |      |      |                                   |      |      |      |      | ×      | ×      | ×      |
| Sagittal abdominal diameter              |   | ×     |         |         |         |                                   |      |      |      |      |                                   |      |      |      |      |        | ×      |        |

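### The blood volume per subject is given as 391.2 / 361.2 ml in the synopsis and section 11.3 but as 436.2 / 406.2 ml in Table 1, a 45.0 ml gap at each site

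*Protocol*

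**What the plan says.** The quantity appears in three places in the current text.

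- **Synopsis, Benefit and risk.** It names its source, "An overview of the blood samples and blood volumes taken during the study is provided in Table 1", and then states: "The total blood volume to be withdrawn from any individual subject will be 391.2 ml for subjects at Veeda Clinical Research, India". The AMC figure in the same sentence is 361.2 ml.
- **Section 11.3.** "The total volume of blood sample is 361.2 ml for AMC subjects and 391.2 ml for Indian subjects". The next sentence reads: "This amount is not considered to be of negative influence to the subject's health". The synopsis makes the same judgement directly after its own totals.
- **Section 8.7, Table 1.** This is the only itemised budget. Its printed totals are 406.2 ml for AMC and 436.2 ml for Veeda (India).

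Exclusion 15 in section 6.3 also bears on the total. One of its limbs excludes a subject if "the total blood loss in the last 3 months, including for this study, exceeds 450 mL".

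**The concern.** The synopsis cites Table 1 and then contradicts it in the next sentence. The two risk sections, which an ethics committee is likely to rely on, both carry the lower pair of figures and attach the reassurance to them. If Table 1 is right, the stated burden is 45.0 ml too low at each site and the safety judgement was made on the wrong volume. If the text is right, a row and both totals in Table 1 are wrong.

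The total may also enter an eligibility rule. Exclusion 15 sets a 450 mL limit that takes in blood drawn for this study. A site that counts the planned volume toward that limit would get a different margin depending on which page it used.

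**Working it through.** **Inputs (Table 1, section 8.7).** Haematology/endocrinology 20 tubes of 4.5 ml; haemostasis 5 of 2.7 ml; biochemistry 5 of 4.5 ml; viral serology 1 of 10 ml; SIRT 3 of 10 ml (India only); two clamp days, each 125.1 ml plus 20 glucose draws of 0.5 ml.

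**Step 1: reproduce Table 1.**

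- Haematology/endocrinology: 20 × 4.5 = 90
- Haemostasis: 5 × 2.7 = 13.5
- Biochemistry: 5 × 4.5 = 22.5
- Serology: 1 × 10 = 10
- Clamp days: 2 × (125.1 + 20 × 0.5) = 2 × 135.1 = 270.2
- AMC: 90 + 13.5 + 22.5 + 10 + 270.2 = **406.2 ml**
- India: 406.2 + 3 × 10 = **436.2 ml**

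Both match the printed totals.

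**Step 2: compare with the synopsis and section 11.3.**

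| Site | Text total | Table 1 total | Gap | Gap as % of Table 1 |
|---|---|---|---|---|
| India | 391.2 | 436.2 | 45.0 | 45 / 436.2 = 10.3% |
| AMC | 361.2 | 406.2 | 45.0 | 45 / 406.2 = 11.1% |

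**Step 3: look for the source of the gap.** Leaving rows out does not reproduce the AMC text figure of 361.2 ml:

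- without clamp glucose: 386.2
- without serology: 396.2
- without biochemistry: 383.7
- without haemostasis and biochemistry: 370.2

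Halving the haematology/endocrinology row does: 10 × 4.5 = 45, and 45 + 13.5 + 22.5 + 10 + 270.2 = 361.2 ml (AMC), plus 30 = 391.2 ml (India). That is the simplest single change that fits. It is an inference; the protocol does not state the cause.

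**Step 4: can the count be settled from the protocol?** Section 8.5.1 says "A blood sample will be taken for measurement of haematology and biochemistry parameters" and lists five time points. Twenty tubes is then 20 / 5 = 4 per visit, and ten tubes is 10 / 5 = 2 per visit; haemostasis and biochemistry each have 1 per visit. Appendix A says "Time points for the clinical laboratory tests are mentioned in Appendix B", but Appendix B, in the text available here, has no endocrinology row to count. The question stays open.

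**Step 5: margin to 450 mL, if the whole planned volume is counted.**

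- India: 450 − 436.2 = 13.8 ml (Table 1), or 450 − 391.2 = 58.8 ml (text)
- AMC: 450 − 406.2 = 43.8 ml (Table 1), or 450 − 361.2 = 88.8 ml (text)

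The 13.8 ml is an upper bound. Table 1 budgets 20 glucose draws per clamp. Ten-minute sampling from 0:00 to about 4:20 (section 8.4.1, Appendix C) implies about 260 / 10 = 26. If the extra six draws are not covered elsewhere in the clamp-day volume, they add 2 × 6 × 0.5 = 6 ml, which leaves 13.8 − 6 = 7.8 ml for an Indian subject on Table 1.

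**The case against.** The mismatch is hard to dispute. PDF reading does not explain it, since the table's rows and totals agree with each other and the lower pair appears identically in two sections. The fair objections concern what follows from it.

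- **Exclusion 15.** A reader might infer that Indian candidates have only 13.8 ml of room at entry. The protocol does not say so. The criterion begins with history and looks back over three months, so at entry it can mean only study blood already drawn, such as the screening samples. The window matters too. Section 5.1 allows up to 12 weeks of screening and 17.5 weeks of participation, so the full volume need not fall within three months; under the 28-day screening limit in section 8.5 it would. This objection stands: the margins in step 5 apply only where the planned total is counted.
- **Which total is right.** A reader might infer that Table 1 must be correct because it adds up. Internal consistency does not verify a tube count, and two tubes per visit for a row covering two test groups is as plausible as four. This also stands. Preferring Table 1 for now is caution, not proof.
- **Consequence.** A reader might infer a breach of 450 mL. All four totals are below it. Nothing in the protocol shows that 45 ml would change the safety judgement, and the consent pages are not available, so nothing can be said about what subjects were told.

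None of this removes the contradiction or the fact that the reassurance is attached to the lower figure.

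**Conclusion.** The point holds as a minor but definite inconsistency. One quantity has two values in the current protocol, 45.0 ml apart at each site, and both risk sections use the value that the only itemised budget does not support. The arithmetic needs no assumption. Attributing the gap to ten haematology/endocrinology tubes is an inference from an exact match. The effect on exclusion 15 is conditional: where planned volume is counted, the Indian margin is at most about 13.8 ml on Table 1 instead of 58.8 ml, and less if clamp glucose draws are under-counted. Study sampling alone does not exceed 450 mL on either stated total. Endpoints, power and analysis are untouched.

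**What to change.** 1. Verify the number of 4.5 ml haematology/endocrinology tubes per visit against the laboratory schedule and, at the same time, the number of glucose draws per clamp.
2. Carry one total per site through the synopsis, Table 1 and section 11.3. Unless the tube count is shown to be ten, state 436.2 ml (India) and 406.2 ml (AMC) in both risk sections, adjusted for any correction to the glucose draws.
3. Make the safety judgement against the total that is kept.
4. Where planned study volume is counted toward the 450 mL limit in exclusion 15, use the verified total.

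The cost is a document correction: a check of counts and one pair of totals aligned in three places. No procedure, endpoint or analysis changes. If Table 1 is confirmed, the burden stated in the risk sections rises by 45.0 ml.

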### 3. INTRODUCTION

#### Background

A plethora of studies have shown that visceral adiposity and insulin resistance are the key underlying factors associated with clustering atherogenic abnormalities which include a typical atherogenic dyslipidemic state (high triglyceride and apolipoprotein B concentrations, an increased proportion of small dense LDL particles and a reduced concentration of HDL-cholesterol with HDL particles also being smaller in size), a prothrombotic profile, and a state of inflammation. Furthermore, visceral adiposity and insulin resistance could also contribute to an elevated blood pressure and to dysglycemia eventually leading to Atherogenic Cardiovascular Disease and Type 2 diabetes Fig 1 describes the pathologies originating from Visceral adiposity and Insulin Resistance.

[figure not shown]

**Fig 1: Pathologies originating from Visceral Adiposity and Insulin Resistance**

The incidence of visceral adiposity and the related comorbidities are increasing worldwide, leading to increased burden of cardiovascular risk in general population. Traditional risk factors as defined by Framingham Heart Study (age, race, gender, smoking, hypertension, High Cholesterol and family history) do not completely account for the cardiovascular risk in majority of population. Non-traditional risk factors (also known as Non-framingham risk factors) such as obesity, insulin resistance, dyslipidemia, dysglycemia and Hypertension are equally important culprit for increase in CV risk. Hence Cardiometabolic risk which is the overall risk of

cardiovascular disease (CVD) and diabetes resulting from the presence of the non-traditional risk factors and also of traditional risk has been described as a plausible target for treatment. Figure 2 elucidates the concept of Cardiometabolic risk.

[figure not shown]

**Fig 2: Concept of Cardiometabolic Risk**

The pathophysiology underlying Cardiometabolic risk is complex and has been only partially elucidated.

There is considerable evidence supporting the notion that excess abdominal fat is predictive of insulin resistance and the presence of related metabolic abnormalities. Studies of the measurement of abdominal adiposity (magnetic resonance imaging and computed tomography) have commonly reached the conclusion that the amount of visceral adipose fat not that of subcutaneous abdominal fat, is a quite dominant correlate of metabolic abnormalities observed in overweight/obese patients

Visceral Adipose tissue (VAT) is not only an energy storage tissue, but also a metabolically active organ secreting hormones, cytokines and growth factors, collectively called as adipocytokines. It is believed that anti-atherosclerotic adipocytokines, such as leptin and adiponectin, and proatherosclerotic cytokines, such as interleukin (IL)-6 and tumor necrosis factor (TNF)- $\alpha$ , cooperatively regulate metabolic and cardiovascular homeostasis at local and remote sites. Visceral adiposity perturbs this homeostasis thus resulting in pro-atherogenic state.

Visceral adiposity is also associated with a pro-inflammatory state which is also an etiological factor for the atherosclerotic process. Overall, these pathophysiological

---

processes culminate into increased risk of ASCVD (Atherosclerotic Cardiovascular Disease)..

Visceral adiposity is an important causative factor for whole body Insulin resistance. Visceral adiposity leads to increased fatty acid load to liver and muscle forming an Insulin resistant milieu in liver and muscle tissues.

Visceral adiposity and associated insulin resistance contributes to exposure of high concentrations of free fatty acids (due to increased lipolysis) to the liver (through the portal circulation), impairing several hepatic metabolic processes leading to hyperinsulinemia (decreased insulin clearance), glucose intolerance (increased hepatic glucose production), and hypertriglyceridemia (increased VLDL-apolipoprotein B secretion).

Intra-hepatic fat thus represents an important contributor to the pathogenesis of Cardiometabolic risk.

In fact various global studies (eg The Framingham Heart Study) have shown that adiposity represented by increased intrahepatic fat (IHF), compared with general adiposity (represented by BMI), would explain more of the variance in cardiovascular disease (CVD) risk factors.

Insulin resistance (IR) is another important component of cardiometabolic risk and consists of two important features; peripheral and hepatic insulin sensitivity. Peripheral insulin resistance leads to decreased insulin stimulated glucose uptake in skeletal muscle and adipocytes. Hepatic IR increases plasma glucose levels by decreasing insulin mediated suppression of glucose production. The physiological mechanisms underlying insulin resistance are complex and not fully elucidated. Amongst others, an impairment of the skeletal muscle metabolic energy transduction pathways (mitochondrial dysfunction) has been suggested to be casually related to insulin resistance. Mitochondrial fatty acid overload and incomplete fatty acid oxidation have been suggested to result in increased availability of fatty acids for lipid accumulation. Fatty acid metabolites are thought to induce insulin resistance in both liver and muscle by impairing the insulin-signaling pathway.

Evidences suggest that Visceral adiposity, one of the most important cardiometabolic risk factors originates from a chronic imbalance between energy intake and expenditure.

---

At the cellular level, various pathophysiological events responsible for metabolic abnormalities have been hypothesized. Among these, impaired cellular metabolism has been suggested as a key pathophysiological process. In particular, defective oxidative metabolism suggesting impairment in mitochondrial function, seems to be involved in visceral fat gain and in the development of insulin resistance, Evidences are emerging to support the concept that alterations in mitochondrial biogenesis and energetics are linked to the development and progression of metabolic disorders and CVD in obesity.

Both obesity and common forms of type-2 diabetes have been found to be associated with reduction in mitochondrial size and number, which in turn results into reduced activity of tricarboxylic acid cycle, E- oxidation, electron transport enzymes and glucose oxidation. In diabetes mellitus, a potential role of deregulation of expression of genes involved in oxidative metabolism has also been suggested by studies in animals and human..

It has also been hypothesized that the abnormally high availability of fat as a substrate for energy leads to reduction in oxidative capacity of mitochondria and hyperinsulinemia.

This vicious cycle of lower energy expenditure leading to accumulation of fat and further reduction of oxidative capacity of mitochondria eventually culminates into visceral obesity, insulin resistance, hypertension, impaired lipid profile, thus overall increased cardiometabolic risk.

There is clearly a significant unmet medical need for safe and effective weight-reducing therapies to prevent the debilitating metabolic diseases and mortality that are associated with increasing central adiposity.

To date, pharmacological agents for the management of Cardiometabolic risk have been limited and unsatisfactory. Most have attempted to address weight reduction by targeting appetite at the central nervous system. So far most of these with central effect have been plagued by a higher incidence of depressive symptoms or have resulted in higher incidence of cardiovascular side-effects.

Thyroid hormones (THs) play an important role in several physiological processes including growth and development in early life as well as metabolic control later in life. The mechanism underlying the calorogenic effects of THs remains to be elucidated. Among the widespread actions of thyroid hormones (THs), increasing

---

metabolic rate and lowering atherogenic serum lipoproteins are clinically interesting metabolic responses since these could hypothetically be of use to treat obesity and its related co-morbidities. However previous attempts to mimic the effects of THs using thyroid hormone metabolites and analogues have been complicated by the induction of thyrotoxic adverse effects in other organ systems such as the heart and skeleton. Consequently, the development of a TH agonist or analogue that retains anti obesity efficacy while being devoid of thyrotoxic effects, would represent a potentially valuable therapeutic approach for obesity related co-morbidity. T2 (3,5-diiodothyronine) is a metabolically active iodothyronine with the capacity to stimulate oxidation of fatty acids in metabolically active tissues (heart, skeletal muscle, liver and Brown adipose tissue) at relatively low concentrations. T2 has lesser affinity towards the thyroid receptor compared to T3 and its metabolic effects are rapid.

TRC150094 is a novel thyromimetic analogous to 3,5-diiodothyronine (T2) being developed by Torrent for the treatment of Cardiometabolic risk associated with non-traditional risk factors.

TRC150094 is a thyromimetic analogous to T2 that aims at increasing the energy expenditure and thus regaining the balance.

In various preclinical studies conducted in multiple animal models of visceral adiposity, insulin resistance and metabolic syndrome, it was found that TRC150094 increases energy expenditure through increase in mitochondrial metabolic activity and attenuates visceral adiposity, atherogenic dyslipidemia, blood pressure and improved insulin sensitivity.

If these effects are replicated in clinical setting, this profile will prove invaluable in the treatment of Cardiometabolic risk associated with visceral adiposity.

Clinically, the continuous administration of TRC150094 administration leading to sustained increase in Energy Expenditure is expected to result in:

- Decrease in adiposity leading to a more desirable body mass composition,
- Decrease in hepatic fat thus improvement in NAFLD,

- 
- Improvement in insulin sensitivity thus improvement in glucose homeostasis,
  - Improvement in insulin sensitivity, dependent renal-hormonal axis (RAAS and SNS), endothelial function and thus, improvement in Blood Pressure profile,
  - Improvement in lipid profile.

Phase 1 Single Dose studies have been completed that included Single Ascending dose study in overweight/obese subjects, food effect study and elderly study. During these studies, TRC150094 has been found to be well tolerated; with safety established up to 400 mg single dose in overweight/obese subjects of age group 18-65 years. Multiple Ascending Dose study is ongoing. There were two sequential dose levels (50 mg OD and 150 mg OD for 28 days) planned for this study. Of these, the first cohort (50 mg OD for 28 days) has been completed and the safety has been established on this dose.

